## Abstract

**Background:**

Aflatoxins (AFs) are naturally occurring fungal metabolites produced by the *Aspergilla* species of fungi. The staple food grain, maize (*Zea mays*), is highly susceptible to AF contamination. In Kenya, contamination of maize supplies by AFs is a recognized public health problem which has resulted in over 600 human deaths. Human exposure to AFs can occur in utero, via breast milk, through weaning foods, and throughout an individual’s lifetime. Recent epidemiological studies have shown that exposure to AFs in early life through diet is a contributing factor to immune suppression, micronutrient deficiency, possible vaccine interference, and impaired growth in children. However, these results remain inconsistent and inconclusive due to lack of randomized controlled studies.

**Methods:**

A randomized school-based cross-sectional study was designed to study AF exposure levels and associated health effects in children between ages 6 and 12 years. Participants were recruited from primary schools within Siaya and Makueni Counties of Kenya, East Africa. The Joint Ethics Committee of the University of Nairobi and Kenyatta National Hospital in Kenya approved the research protocol and procedures for the study. Both parental consent and child assent were obtained before enrollment in the study. Parents were requested to provide household grain samples and fill out questionnaires detailing their sociodemographic information, household dietary patterns, farming practices, and knowledge of AF contamination. Blood samples were collected from children participants, and sera were prepared for analysis of AFB_1_-lysine which is one of the validated biomarkers for AF exposure.

**Discussion:**

This protocol describes a school-based, cross-sectional study whose objective is to comparatively evaluate the role of AF exposure on adverse health outcomes in children. Specifically, effects of cumulative AF exposure on nutritional status, immune markers, and growth parameters will be assessed.

**Trial registration:**

This study is not a clinical trial, rather a cross-sectional study aimed at providing baseline data on AF exposures in children who live in presumably high versus low AF exposure regions. Results from the study can be used to design interventions and/or prospective cohort studies aimed at studying adverse health effects associated with cumulative AF exposure through diets. The study reference number is P741/12/2017 and registered with KNH-UoN Ethics and Research Committee.

## Background

Aflatoxins (AFs) are a group of naturally occurring mycotoxins produced by the common fungus *Aspergillus flavus* and the closely related *Aspergillus parasiticus* fungi [1–3]. Up to 4.5 billion people around the world are exposed to AFs through the diet and/or via occupational exposures during grain handling [4, 5]. AFs are common food contaminants which present a persistent challenge throughout the food chain. Food staples frequently contaminated with AFs include maize, peanuts, rice, cassava, spices, and other food items [1–3].

There are up to 14 different groups of naturally occurring AFs, but the commonly studied groups include B_1_, B_2_, G_1_, and G_2_ [1, 3]. Aflatoxin B_1_ (AFB_1_) is the most biologically potent because it is a confirmed human carcinogen classified into group I by the International Agency for Research on Cancer [2, 3]. AFB_1_ is a major risk factor associated with primary liver cancers as evident in many studies conducted in Africa and South East Asia [6–8]. Moreover, AFs are immune toxicants and have been associated with immune suppression in human populations [9, 10]. In children, recent epidemiology studies provide evidence that cumulative exposure to AFs in low concentrations contributes to micronutrient deficiency, possible vaccine interference, immune suppression, and growth impairments [11–13]. The adverse health outcomes associated with AF exposure may persist into adulthood if neither interventions nor corrective measures are undertaken. To date, comprehensive data on AF exposure is limited, and thus, assessment of adverse health outcomes is further hindered.

Contrary to long-term exposure to AFs where adverse health outcomes occur over time, dietary exposure to AFs exceeding 200 μg/kg in the short term can be fatal due to aflatoxicosis [14–16]. Aflatoxicosis is a medical condition characterized by jaundice, bile duct proliferation, edema, sudden liver failure, and ultimately death within 24 h of consumption of AF-contaminated maize [15–18].

In Kenya, AF contamination in maize supplies is a recognized public health problem, which has resulted in more than 600 documented human deaths attributed to aflatoxicosis [19–21]. The US Food and Drug Administration (USFDA) recommends that food destined for human consumption should not exceed total AFs of 20 μg/kg [22]. The European Union’s Codex Alimentarius recommends 15 μg/kg [23] while Kenya, given its troubled past with deaths associated with aflatoxicosis, stipulated a strict recommendation of 10 μg/kg [24]. These recommended exposure levels are significantly difficult to implement due to widespread subsistence farming which promotes higher AF exposure because maize produced in farms are consumed directly without prior testing for AF contamination levels.

### Study hypotheses, objective, and specific aims

We hypothesize that children recruited from high AF exposure region of Makueni are more likely to suffer adverse health outcomes including micronutrient deficiency, immune suppression, and growth impairment compared to children recruited from low exposure region of Siaya County. This hypothesis will be tested against the null hypothesis of dietary exposure to AFs is not associated with adverse health outcomes in children.

The general objective of the study is to provide a comprehensive assessment of how dietary exposure to AFs contributes to micronutrient deficiency, immune suppression, and growth impairment in school-going children. Specific aims include the following: (1) to determine the cumulative levels of AF exposure in children of Makueni and Siaya Counties; (2) to determine the nutritional and immune status of children in Siaya and Makueni Counties; (3) to study the association between AF exposure, micronutrient deficiency, and immune suppression; and (4) to elucidate possible growth impairment, if any, in children with high AFB_1_-lysine adducts exceeding 10 pg/mg of albumin.

This study will be the first to provide baseline data on AF exposure in children between the ages of 6 and 12 years recruited from a high and low AF exposure regions of Kenya. The study is a collaborative project between the University of Nairobi’s KAVI Institute of Clinical Research and the University of Georgia in Athens in the USA. The study protocol is based on the SPIRIT (Standard Protocol Items: Recommendations for Interventional Trials) and CONSORT 2010 (Consolidated Standards of Reporting Trials) reporting guidelines.

## Methods/design

The study design is school-based and cross-sectional to provide a snapshot of AF exposure levels among children recruited from Siaya and Makueni Counties. Cross-sectional study design was preferred due to its ability to generate factual information on AF exposure among children widespread over two geographic locations. To ensure samples are representative of both Makueni and Siaya Counties, primary schools without feeding programs were randomly selected in different constituencies per county.

### Setting of the study

The selection of Makueni and Siaya Counties was made according to previous studies which reported high AF exposures in Makueni County while Siaya’s exposure levels were below the level of detection [15, 25]. Makueni County lies in Kenya’s former Eastern Province while Siaya County forms one of the six counties in the former Nyanza Province [25]. Siaya County is hot and humid with temperatures averaging from 21 to 25 °C while annual precipitation ranges between 1000 and 1750 mm [26]. Conversely, the climate of Makueni County is predominantly semi-arid characterized by long dry seasons interspersed by an annual rainfall of about 500 mm and ambient temperature ranges between 18 and 24 °C in the cold season and between 24 and 33 °C in the hot season [27]. Makueni County’s aridity has been implicated to be a significant contributing factor to AF contamination as a result of undue crop stress [15, 27]. The Luo ethnic groups are the main inhabitants of Siaya County while the Akamba community inhabits the high exposure regions of Makueni County [28]. The estimated poverty rate in Makueni and Siaya Counties is 64% and 48%, respectively, compared to the national average of 47% as of 2009 [26, 28]. Overall, the choice of Makueni and Siaya Counties as study location provides control for differences in weather conditions, ethnicity, and poverty levels.

Due to limited food diversity in sub-Saharan Africa, our study populations depend on maize and maize-based products for daily energy requirements [29, 30]. The dietary staples in Kenya include maize-based meals comprised of solid maize meal, commonly known as *ugali* in Swahili; porridge; roasted and boiled maize cobs; and/or maize boiled with beans [30]. Moreover, each household is estimated to consume maize-based meals at least two times a day because *ugali* is often served during lunch and/or dinner in accompaniment with a mix of vegetables and/or any kind of stew [30, 31]. Consuming a variety of foods from several food groups is a recommended approach to achieve necessary nutritional requirements and limit excessive exposure to AFs through the diet [32]. Diet diversification has been proposed to be instrumental in mitigating AF exposure and the associated adverse health outcomes. The International Food Policy Research Institute proposed that households with a dietary score less than 4.5 can be categorized as low dietary diversity, a score between 4.5 and 6 has medium dietary diversity, and a score greater than 6 can be considered both high and good dietary diversity [33]. In our study populations, past studies reported low dietary diversity with a score of less than 4 food groups each day [31, 34]. Therefore, food insecurity is paramount in our study populations due to low agricultural productivity that is characterized by unreliable rains, limited access to farm inputs, and hired labor which increases the cost of food production significantly [26]. Nonetheless, small-scale holder farmers undertake maize cultivation for household consumption despite low agricultural output and increased risk of AF contamination.

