#### Human participants

School administrations were requested to convene parent meetings at a convenient time and location for participants. Community leaders including local area chiefs and members of the county assembly were invited to the meetings. The chairperson of the Parent Teachers Association was in attendance and presided over the meetings. The study purpose and significance were explained to school officials, teachers, support staff, and parents. The participants were given ample opportunity to ask questions during the meeting, before subject recruitment, and during the study to ensure full disclosure of study components. Informed consent forms were explained to parents in their local dialect, and all their questions were addressed before being asked to provide consent and fill out questionnaires.

The five-part questionnaire administered collected basic information including participants’ age, sex, weight, height, and mid-upper arm circumference; sociodemographic factors including marital status, education levels, living conditions, occupations of both the respondent and their spouse, household income levels, and information on home ownership and living conditions. Participants also reported farming practices which entail whether they grow or buy maize for household use, use of pesticides and/or fertilizers during farming, extent of AF knowledge, and how each household stores maize and other food supplies after harvest. In addition, the questionnaire collected information on dietary intake of different food groups, number of meals in a day, food choice, and nutrition practices. Information collected from questionnaires provided sufficient information to enable analysis of socioeconomic status and respective poverty levels. Moreover, these possible confounding factors can be easily controlled in statistical analyses.

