## Conclusions

This paper describes a protocol of the first school-based randomized cross-sectional study aimed at assessing health effects associated with exposure to AFs through the diet. Whether or not a relationship is found between AF exposure and adverse health outcomes, the results can be used to prioritize AF control efforts not only in Kenya but also in other developing countries.

The strength of the study is its multifaceted approach in assessing health effects in children exposed to AFs through the diet. In addition, recruiting subjects from both a high and a low exposure region is instrumental in elucidating the role of AF exposure specifically on micronutrient deficiency, immune suppression, and possible growth impairments.

In conclusion, exposure to AFs and other mycotoxins in low- and middle-income countries has been shown to contribute to immune suppression and growth impairment. Mycotoxins are also suspected to interfere with vaccine efficiency making children more vulnerable to increased risk of infectious diseases. Pediatricians and clinicians in developing nations should pay attention to the role of not only AFs but also other environmental factors that influence health in their practice to better serve their populations.

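### The article says the choice of counties controls for weather, ethnicity and poverty, but the counties differ on all three, so the hypothesised Makueni–Siaya contrast cannot isolate aflatoxin.

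*Protocol article*

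**What the plan says.** The section on the setting of the study describes the two counties and concludes: "Overall, the choice of Makueni and Siaya Counties as study location provides control for differences in weather conditions, ethnicity, and poverty levels". The facts just before that sentence are these.

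- **Weather.** "Siaya County is hot and humid with temperatures averaging from 21 to 25 °C while annual precipitation ranges between 1000 and 1750 mm". Makueni is described as mainly semi-arid, with about 500 mm of rain a year, and its aridity is named as a contributor to contamination.
- **Ethnicity.** "The Luo ethnic groups are the main inhabitants of Siaya County while the Akamba community inhabits the high exposure regions of Makueni County".
- **Poverty.** 64% in Makueni and 48% in Siaya.

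The section on hypotheses and aims proposes that "children recruited from high AF exposure region of Makueni are more likely to suffer adverse health outcomes" than children from Siaya, and tests this against the "null hypothesis of dietary exposure to AFs is not associated with adverse health outcomes in children". Aims 3 and 4 are framed on exposure and on an AFB1-lysine threshold, not on county. The laboratory and data analysis section plans adjustment for socioeconomic factors and other possible confounders. The Conclusions say that "recruiting subjects from both a high and a low exposure region is instrumental in elucidating the role of AF exposure specifically" on the three health outcomes.

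**The concern.** Choosing two sites that differ on a factor does not control for that factor. It ties the factor to whatever else distinguishes the sites, which here is the exposure label. The article therefore claims a design property that its own description contradicts. That is a misstatement, not a detail left to an analysis plan.

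It matters because the stated hypothesis is a comparison of counties, while the null is about dietary aflatoxin. These are different propositions. If children in the two counties differ in growth, immune markers or micronutrients for reasons unrelated to aflatoxin, the comparison can reject the null and say nothing about aflatoxin. The Conclusions intend the results to guide the priority of aflatoxin control in Kenya and elsewhere, so a misattributed county difference would have consequences.

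**Working it through.** **1. The three factors side by side** (all from the section on the setting of the study)

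| Factor | Makueni (high) | Siaya (low) | Difference |
|---|---|---|---|
| Annual rain | about 500 mm | 1000–1750 mm | 1000/500 = 2 to 1750/500 = 3.5 times |
| Main ethnic group | Akamba | Luo | different |
| Poverty | 64% | 48% | 16 points; odds ratio (0.64/0.36)/(0.48/0.52) = 1.93 |

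None of the three is balanced. Main ethnic group and climate vary almost only between counties, and there is one county per exposure level, so no covariate adjustment can separate them from the county label. Poverty varies within each county.

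**2. The number per county**

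The printed formula, with X² = 3.841, P = 0.5, d = 0.05 and N = 842,304 (Siaya), gives 808,822.4 / (2,105.76 + 0.96) = 383.9, so 384. Makueni also gives 384. The stated 393 is 2.3% higher. Nothing here turns on that gap, and 393 is used below as the planned number.

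**3. How readily the county contrast rejects with no aflatoxin effect**

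Take a continuous outcome with SD 1 and independent children. The standard error of the county difference is √(2/393) = 0.0713. For a non-aflatoxin difference δ, the rejection probability is about Φ(δ/0.0713 − 1.96).

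- δ = 0.1 SD: Φ(1.40 − 1.96) = 29%
- δ = 0.2 SD: Φ(2.80 − 1.96) = 80%
- δ = 0.3 SD: Φ(4.21 − 1.96) = 99%

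A simulation with 2,000 replicates gave 30%, 80% and 99%. The article gives no value for δ, so these are assumptions.

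**4. What the documented poverty gap alone could do**

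This uses a binary outcome, no aflatoxin effect and assumed prevalences. With 50% in poor and 20% in non-poor children, Makueni has 0.64 × 0.50 + 0.36 × 0.20 = 39.2% and Siaya has 0.48 × 0.50 + 0.52 × 0.20 = 34.4%. The difference is 4.8 points, and an unadjusted comparison rejects in about 29% of studies. With 30%/20% the rejection rate is about 8%, and with 60%/20% it is about 44%. The nominal rate is 5%.

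**5. What including county costs**

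The Makueni median is taken as 7.87 pg/mg, the former Eastern Province figure. The Siaya median (0.5 pg/mg) and the geometric standard deviation (GSD, 3) are assumed.

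- Within-county variance of log adduct: (ln 3)² = 1.21
- Between-county variance: [ln(7.87/0.5)/2]² = (2.756/2)² = 1.90
- Total: 3.11

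A county term gives up 1.90/3.11 = 61% of the log-exposure variance. Intervals widen by √(3.11/1.21) = 1.6 compared with a model without county.

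Over Siaya medians of 0.2 to 2 and GSD of 2 to 4, the factor √(1 + [ln(7.87/m)/2]²/(ln GSD)²) runs from √(1 + 0.469/1.922) = 1.1 (m = 2, GSD 4) to √(1 + 3.372/0.480) = 2.8 (m = 0.2, GSD 2).

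**The case against.** Several counterarguments carry weight, and they limit how far the point goes.

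- **Individual exposure is measured.** Aims 3 and 4 use it, and adjustment is planned. This stands, so the defect lies in the county contrast and in the claim made for it, not in the biomarker aims as such.
- **The article disclaims cause and effect.** It does so under Study limitations, but the reason given is that participants may not be contacted again. County confounding is not mentioned, so the disclaimer does not cover this point.
- **Poverty is not inseparable.** The rates overlap, and the questionnaire measures socioeconomic status per household. This stands. Poverty is imbalanced but partly adjustable.
- **Climate is a cause of contamination.** Part of its effect therefore runs through aflatoxin. It can also affect diet and food supply, so it is not only a cause of exposure.
- **The 80% figure is simply the power of a comparison with 393 per group.** That is correct. It shows how readily a modest county difference is detected, not how large the difference is.

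A reader might also infer more than the article supports.

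- **That both exposure labels rest only on province data.** For Makueni, the article cites county-level evidence, including its share of the 2004 outbreak. The province survey bears mainly on Siaya's low label.
- **That "these possible confounding factors can be easily controlled in statistical analyses" covers ethnicity and climate.** The phrase refers to the questionnaire items listed before it, which include neither.
- **That the biomarker models will omit county, or that any county difference will be reported as an aflatoxin effect.** Under the assumptions in step 5 and δ = 0.2 SD, a pooled log-adduct regression without county would reject in about 59% of studies. The article does not say that county will be left out, and model terms are commonly fixed in an analysis plan.

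**Conclusion.** The point holds for the county contrast. The sentence claiming control is contradicted by the facts in its own section. The hypothesis and its null do not match, so rejecting the null on a county difference would not be evidence about aflatoxin. Main ethnic group, climate and unmeasured county factors cannot be separated from exposure in that contrast; poverty can be removed in part.

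The size depends on a quantity the article does not give. A non-aflatoxin county difference of 0.1, 0.2 or 0.3 SD would be declared significant in about 29%, 80% or 99% of studies, ignoring school clustering. The contradiction itself needs no assumption. The finding does not show that the biomarker analyses are biased as planned.

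**What to change.** 1. Withdraw the sentence claiming control, and name ethnicity, climate and poverty as confounders of the county contrast.
2. Restate the hypothesis on individual dietary exposure, so that it matches its null.
3. For aims 3 and 4, base inference on the association of individual AFB1-lysine with each outcome in models that include county, or on within-county slopes combined. Adjust for the household socioeconomic and dietary intake data already collected.
4. Report the Makueni–Siaya contrast as descriptive, and say that it cannot be attributed to aflatoxin.
5. Qualify the statement in the Conclusions that recruiting from two regions shows the specific role of aflatoxin.

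The wording in the Human participants section about questionnaire confounders can stay.

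No new data are needed, and the article describes laboratory work as ongoing and modelling as still to come. The cost is precision: intervals about 1.6 times wider under the stated assumptions (1.1 to 2.8 over the range examined). If most Siaya values are below detection, as the earlier survey suggests, that county adds little to the slope and the inference rests mainly on Makueni. The article should say so.

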### Justification of Makueni and Siaya Counties as study sites

In Kenya’s former Eastern Province, high level of AF contamination is concentrated in Makueni County as evident in multiple aflatoxicosis outbreaks previously reported [15, 18]. In 2004, a severe aflatoxicosis outbreak characterized by 317 cases of acute hepatic failure and subsequent 125 deaths was reported [17, 35, 36]. The Kenyan Ministry of Health worked collaboratively with experts from the US Center for Disease Control and Prevention to assess risk factors associated with the outbreak [18, 21]. While the cases were inhabitants of Makueni, Kitui, and Machakos Counties, inhabitants of Makueni County were the most affected, accounting for almost 50% of the cases [20, 37]. Consumption of AF-contaminated maize was linked to aflatoxicosis [21, 36].

In a serological survey to evaluate regional variation of AF exposure in Kenya, 78% of archived serum samples had detectable AF levels [25]. The highest AF exposure was recorded in the former Eastern Province with a median of 7.87 pg/mg AF albumin adducts, while in the former Nyanza Province, the AF albumin adducts were below the limit of detection (< LOD) in human serum samples evaluated. The AF levels were much lower in all the other five provinces. The regional variation of AF exposure levels as reported by Yard et al. [25] is exhibited in Fig. 1 created using vector map outlines from Vemaps.com [38].

